#### Heterogeneity analysis

### Interpatient heterogeneity

Test-retest variability of PET using modern machines is ~15% (62-64). Therefore, uptake difference between patients (interpatient heterogeneity) is defined as SUV differences of 15% or greater.

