# OBJECTIVES AND HYPOTHESES

## Primary objectives & hypotheses

1. To investigate heterogeneity in tumor uptake of [^18^F]BMS-986192 between patients and within tumor lesions of the same patient (primary tumor and TDLN/lymph node metastases) before treatment, in relation to changes in [^18^F]-FDG uptake before and on treatment

*Hypothesis: interpatient and intrapatient heterogeneity in tumor accumulation of [^18^F]BMS-986192 is expected and can be visualized. [^18^F]-FDG allows identification of viable tumor.*

2. To investigate the feasibility and safety of neoadjuvant nivolumab immunotherapy prior to surgery for locally advanced oral cancer.

*Hypothesis: neoadjuvant immunotherapy with nivolumab is feasible and safe, and will lead to immune activation and clinical response in a subset of patients.*

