## Sample size calculation

Since this is a pilot feasibility study to investigate safety and tolerability, [^18^F]BMS-986192 and [^18^F]-FDG PET imaging before and on treatment with nivolumab, a sample size of 15 evaluable patients has been chosen. The objective of this study is descriptive and hypothesis generating, so no formal statistical justification for the sample size is provided.

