## Secondary study parameters/endpoints

#### Heterogeneity analysis

#### Interpatient, intrapatient and intratumor SUV heterogeneity.

Correlation between both PET scans, and between imaging and response

The correlation between SUV for [^18^F]BMS-986192 and [^18^F]-FDG baseline and on treatment and early response evaluation with [^18^F]-FDG.

Correlation between PET data and Blood/Tissue markers

The correlation between continuous values as SUV and the categorical variables tissue PD-1 and PD-L1 IHC will be assessed for each tumor lesion. Correlation with immuno-monitoring analysis in tumor tissue/lymph nodes and blood, plasma vesicle miRNAs from blood, as well as DNA/RNA profiling in tumor tissue at baseline and at surgery will be assessed.

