### Intrapatient heterogeneity

Tracer uptake differences between lesions of the same patient depend on multiple aspects. These are both biological (e.g. the level of perfusion and target expression), as well as technical (e.g. partial volume and tumor motion effects). True biological differences between lesions that correlate with tumor biology are therefore difficult to define. Because of this, intrapatient uptake differences will be assessed qualitatively.

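### The 15% cut-off for interpatient heterogeneity equals the stated test-retest variability, so it does not separate differences between patients from measurement noise

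*Protocol*

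**What the plan says.** Section 9.2.1 gives its premise as "Test-retest variability of PET using modern machines is ~15% (62-64" (the bracketed numbers are a citation) and concludes from it that "uptake difference between patients (interpatient heterogeneity) is defined as SUV differences of 15% or greater". It does not state:

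- which repeatability statistic the 15% is;
- which SUV measure or lesion is compared;
- whether patients are compared in pairs or with a cohort mean;
- what the percentage is relative to.

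Section 9.2.2 handles the other level differently: "intrapatient uptake differences will be assessed qualitatively".

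Heterogeneity between and within patients is the subject of primary objective 1 in section 2.1, whose hypothesis reads "interpatient and intrapatient heterogeneity in tumor accumulation of [^18^F]BMS-986192 is expected and can be visualized". Section 6.2 nevertheless lists "Interpatient, intrapatient and intratumor SUV heterogeneity" among the secondary parameters. On size, section 4.3 says "a sample size of 15 evaluable patients has been chosen" and adds: "The objective of this study is descriptive and hypothesis generating, so no formal statistical justification for the sample size is provided".

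**The concern.** Two scans of the same uptake differ by an amount that test-retest variability describes. If the line for a real difference between patients is drawn at that same amount, part of what it labels as heterogeneity is measurement error. How large a part depends on what 15% means, because repeatability is reported in several ways that differ by a factor of almost three. The reader cannot look this up. In the protocol's reference list, entries 62 to 64 concern DNA copy-number analysis, a neoantigen pipeline and the genetics of response to CTLA-4 blockade. The figure is also given for PET in general, not for [18F]BMS-986192.

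At stake is the descriptive answer to the interpatient part of objective 1. A report that patients differed by the protocol's definition would say little about whether tracer uptake varies between them.

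**Working it through.** **Inputs.** Cut-off 15% and test-retest variability of about 15% (section 9.2.1). n = 15 (section 4.3), hence 15 × 14 / 2 = 105 pairs. The protocol derives no figure that could be reproduced; the cut-off is simply the test-retest figure.

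**Assumptions.** All 15 patients have the same true SUV and are scanned once. The only variation is measurement error with within-subject CV w. Since the protocol does not define the 15%, four readings are run:

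- (a) it is w itself: w = 15%
- (b) it is the mean absolute test-retest difference: w = 15% / 1.128 = 13.3%
- (c) it is the SD of test-retest differences: w = 15% / √2 = 10.6%
- (d) it is the 95% repeatability limit: w = 15% / (1.96 × √2) = 5.4%

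**One given pair.** The difference of two scans, relative to the pair mean, has SD √2 × w, so P(difference ≥ 15%) = 2 × [1 − Φ(0.15 / (√2 × w))].

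- (a) 0.15 / 0.212 = 0.707, giving 0.48
- (b) 0.15 / 0.188 = 0.798, giving 0.42
- (c) 0.15 / 0.150 = 1.000, giving 0.32 (0.31 with lognormal error)
- (d) 0.15 / 0.0765 = 1.960, giving 0.05

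The denominator is also unstated. Relative to the smaller value, the four results become 0.51, 0.46, 0.35 and 0.07.

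**The whole cohort.** Simulation of 200,000 studies of 15 patients, with normal and lognormal error:

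| Reading | Any of 105 pairs ≥ 15% apart | Any patient ≥ 15% from the cohort mean | 95th percentile of the largest pairwise difference |
|---|---|---|---|
| (a) | 1.000 | 0.99 | 69% |
| (b) | 1.000 | 0.98 | 61% |
| (c) | 0.9996 | 0.89 | 50% |
| (d) | 0.82 | 0.06 | 26% |

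The any-pair and percentile columns are relative to the pair mean. With other denominators the any-pair result stays at about 0.999 or more for (a) to (c) and runs from 0.72 to 0.89 for (d). The last column is the cut-off that noise alone would exceed in only 5% of such studies.

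**The other extreme.** Section 1.1.4 gives lesion SUVs for this tracer in NSCLC of 3.4 ±2.9 and 7.1 ±6.0. If ± is an SD (an assumption), the CVs are 2.9 / 3.4 = 0.85 and 6.0 / 7.1 = 0.85. If patients here varied that much (a second assumption), the SD of log SUV would be √ln(1 + 0.85²) = 0.74. Then 0.15 / (√2 × 0.74) = 0.14, and about 89% of pairs would exceed 15%. Some pair is therefore almost certain to be labelled when true spread is large, and is also very likely to be labelled when there is none.

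**A per-pair limit.** The 95% limit for the difference of two single scans is 1.96 × √2 × w = 2.77 × w, which is 42%, 37%, 29% and 15% for (a) to (d). Reading (d) is the only one on which the present cut-off is that limit. Such a limit does not protect the whole set of pairs. Under (a), with 42% as the cut-off and identical uptake, some pair is still flagged in about 80% of studies (relative to the pair mean) to 95% (relative to the smaller value).

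**The case against.** The best defence is that the study is openly descriptive. It has no alpha, test or success rule, and section 9.2.1 does not say that one pair out of 105 is enough. On reading (d) the label has a conventional 5% error per pair, and only a 6% chance of marking any patient against the cohort mean. This stands, and it limits the point to what the label can show.

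A reader might infer that the primary hypothesis is bound to be confirmed, or that objective 1 cannot fail. The documents do not support that. The objective is to investigate, its hypothesis also has an intrapatient part that the 15% rule does not touch, and near-certainty needs both an any-pair rule and one of readings (a) to (c). None of these is stated.

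A reader might also count the qualitative intrapatient assessment as an error. Section 9.2.2 gives biological and technical reasons for it, and lesion SUVs are measured in any case, so it is a reasoned choice.

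The citation mismatch is probably stale numbering: section 5.5.1 has similar round-bracket numbers, unlike the square brackets used elsewhere. It matters only because it leaves the meaning of 15% untraceable.

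Finally, the NSCLC values are per lesion, from 7 patients in two IHC groups. If they are a guide, true differences may be well above noise. That lessens the practical harm but does not make the cut-off informative.

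Descriptive status removes the need for a power calculation. It does not justify a yes/no label that reports noise as a finding.

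**Conclusion.** The point holds in a limited form. The 15% label cannot distinguish interpatient heterogeneity from measurement noise, because the cut-off is the noise figure itself and that figure is neither defined nor traceable. With identical true uptake, about a third to a half of pairs would be labelled different on three of the four readings, and about one in twenty on the fourth. The any-pair chances apply only if a single pair is taken as evidence of heterogeneity. All figures assume independent normal or lognormal error and one scan per patient.

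The consequence is a possibly misleading description of one part of a primary objective. No confirmatory conclusion is at risk. The protocol itself fixes the rule and its rationale, so this is not a detail left to a statistical analysis plan.

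**What to change.** In section 9.2.1, replace the 15% dichotomy with an estimate: the between-patient SD (or CV) of log SUV with a confidence interval, from a mixed model over the measured lesions with a random patient effect. Show beside it the measurement SD implied by a test-retest figure that is correctly cited and whose statistic is named. The comparison is needed because, with one scan per time point, the within-patient term mixes lesion differences with noise, and any error common to a whole scan falls into the between-patient term.

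If a pairwise flag is kept, set it at 2.77 × the within-subject CV, state the denominator, and describe it as a per-pair limit with about 5% error per pair. A single flagged pair among 105 should not be read as evidence of heterogeneity; a 5% limit for the whole study would lie at about 26 to 69%, depending on what 15% means.

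The cost is a rewording and a standard model on data already planned. The drawback is imprecision. With one value per patient and 14 degrees of freedom, a 95% interval for an SD runs from √(14 / 26.12) = 0.73 to √(14 / 5.63) = 1.58 times the estimate. A wide interval is the honest description of what 15 patients can show.

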### Intrapatient heterogeneity

Tracer uptake differences between lesions of the same patient depend on multiple aspects. These are both biological (e.g. the level of perfusion and target expression), as well as technical (e.g. partial volume and tumor motion effects). True biological differences between lesions that correlate with tumor biology are therefore difficult to define. Because of this, intrapatient uptake differences will be assessed qualitatively.

### Intratumor heterogeneity

Uptake heterogeneity within a tumor also depends on multiple aspects. It can be the result of biological differences, such as perfusion (the tracer is not able to reach some parts of the tumor), true target expression or tumor necrosis. Tumor motion effects also influence intratumor heterogeneity since PET acquisition is not respiratory gated.

Intratumor heterogeneity is defined as the ratio of SUV_max_ : SUV_mean_. The level will be calculated on a linear scale.

## Correlation between PET data and response

The correlation between the continuous variable SUV, the % change in SUV and TLG and the categorical variables response on imaging (according to RECIST 1.1 CR, PR, SD, PD and CMR, PMR, SMD and PMD according to PERCIST) and pathological response (according to the Mandard Classification System, Table 3) will be assessed.

**Table 3** Mandard Classification system for Tumor Regression Grading (TRG) [69, 70]

| **Descriptive** |  |  |
| --- | --- | --- |
| Complete regression | TRG 1 | No residual cancer cells |
| Subtotal | TRG 2 | Rare cancer cells |
| Partial | TRG 3 | Fibrosis outgrowing residual cancer |
| No regression | TRG 4 | Residual cancer outgrowing fibrosis |
|  | TRG 5 | Absence of regressive change |

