### [18F]-FDG PET

As the treatment of HNSCC patients often involves multimodality treatment with surgery, radiotherapy and concomitant systemic therapy which causes extensive morbidity, early response evaluation could significantly improve quality of life and potentially survival as treatment can be adapted accordingly. A study with induction chemotherapy indeed showed promising results for predicting response in patients with significant reduction in the [18F]-FDG uptake in all lesions expressed as total lesion glycolysis (responders -85.9% ± 18.6 vs non-responders 36.4±64.1) [39]. In a meta-analysis the same conclusion was reached, early [^18^F]-FDG shows promise for response predication, however, standardized evaluation is required for further conclusions [40].

Regarding the usefulness of early [^18^F]-FDG imaging for patients treated with immunotherapy there is only limited evidence in literature so far. For patients with melanoma treated with a variety of immunotherapies including nivolumab [^18^F]-FDG changes showed mainly increase in [^18^F]-FDG uptake at 3 weeks after start of treatment in patients who responded at the later evaluation time points. These findings are consistent with immune activation in the tumor leading to increased glucose consumption [41].

Based on these results, early increase in [^18^F]-FDG uptake in patients with locally advanced oral cancer treated neoadjuvantly with nivolumab are expected to predict histopathological response in the resection material.

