### Rationale for endpoints

This is a feasibility study of neoadjuvant nivolumab in locally advanced oral cancer combined with [^18^F]BMS-986192 and [^18^F]-FDG PET as well as immuno-monitoring and DNA profiling on tissue and blood in order to identify biomarkers for response and investigate safety.

The primary endpoint of this study is [^18^F]BMS-986192 uptake in tumor lesions and safety and tolerability of neoadjuvant nivolumab. [^18^F]BMS-986192 tumor uptake will be quantified, tumor uptake heterogeneity between patients and within and between tumor lesions of the same patient will be assessed. These results will be correlated with [^18^F]-FDG uptake, as effective treatment with immune therapy may lead to increase in early [^18^F]-FDG uptake, as well as to (pathological) response.

The secondary endpoints include the correlation of the imaging and response data to measured blood and tissue parameters. The immune status will be assessed in the tumor by multiplex immunostaining (see section 3.10.1) and in peripheral blood and TDLN by flowcytometry for the frequency and activation status of immune subsets (see section 3.8). Cytokine profiling may be performed in plasma or from TDLN in ex vivo O/N cultures.

In addition, the presence of neoantigens and the molecular background of the tumor as copy-number-high or copy-number-silent will be determined. Neoantigen analysis will be performed by DNA sequencing using a combined approach of low coverage whole genome sequencing for copy numbers, and exome enrichment sequencing for mutations. Normal DNA from blood will be analyzed in parallel to filter SNPs. In addition RNA sequencing will be performed and the data mined as previously described [53].

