## Response evaluation

Patient will have a standard MRI of head and neck at screening (day -5-0, figure 1) and just before surgery (day 24 ±3-27, figure 1) to evaluate the response to nivolumab.

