### [^18^F]-FDG PET

Data-analysis will be done using in-house developed software, including SUV_max_, SUV_peak_, 70% VOI, 50% VOI, normalized for serum glucose and body weight. Metabolic tumor volume (MTV is defined with an isocontour VOI of 50% of SUV_peak_ with background correction) and total lesion glycolysis (TLG is defined as SUV_mean corrected for body weight_ times MTV). Early response will be categorized according to PERCIST [67].

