**APPENDICES**

# APPENDIX 1: Response Evaluation Criteria in Solid Tumors (RECIST) 1.1 Criteria for evaluating Response in Solid Tumors

RECIST version 1.1* will be used in this study for assessment of tumor response with CT as the preferred imaging technique in this study.

* As published in the European Journal of Cancer:

E.A. Eisenhauer, P. Therasse, J. Bogaerts, L.H. Schwartz, D. Sargent, R. Ford, J. Dancey, S. Arbuck, S. Gwyther, M. Mooney, L. Rubinstein, L. Shankar, L. Dodd, R. Kaplan, D. Lacombe, J. Verweij. New response evaluation criteria in solid tumors: Revised RECIST guideline (version 1.1). Eur J Cancer. 2009 Jan;45(2):228-47.

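### Correlating FDG change with PERCIST class (9.3) is circular, and the PERCIST labels may run against the early FDG rise the protocol expects when treatment works

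*Protocol*

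**What the plan says.** - **Analysis (9.3).** SUV and "the % change in SUV and TLG and the categorical variables response on imaging" are to be correlated with response, graded "according to RECIST 1.1 CR, PR, SD, PD and CMR, PMR, SMD and PMD according to PERCIST". The same sentence adds pathological response by Mandard grade.
- **Source of the PERCIST class (5.5.2).** Under FDG PET: "Early response will be categorized according to PERCIST". The FDG scans are made at baseline and about 21 days after nivolumab (3.2, 5.3).
- **TLG (9.1).** TLG is determined for FDG only.
- **Endpoint (6.2).** SUV of both tracers, "baseline and on treatment and early response evaluation with" FDG, so the pairing appears here too.
- **Expected direction.** Section 1.2.7 says "effective treatment with immune therapy may lead to increase in early" FDG uptake. In 1.2.2, early increases "are expected to predict histopathological response in the resection material".
- **RECIST.** Appendix 1 applies RECIST 1.1 "with CT as the preferred imaging technique in this study". Section 3.5 states "Patient will have a standard MRI of head and neck at screening", repeated just before surgery. Section 7.12 and the schedule (7.19) place the diagnostic CT before treatment only.

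**The concern.** Two features of 9.3 work against its purpose.

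First, a PERCIST class is a coarse version of the change between two FDG scans. Correlating FDG change with it correlates a measurement with its own categories, so a strong result is assured and says nothing about tumor kill. Secondary hypothesis 5 (2.2) says early FDG changes will allow early response prediction but does not name the response standard. A built-in association could therefore be offered as support.

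Second, the class names run from complete metabolic response to progression, while the protocol expects uptake to rise when nivolumab works. Nothing says how an early rise is to be read beside a PERCIST label. A genuine immune flare could be tabulated as stable or progressive disease.

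The study is meant to identify biomarkers worth taking into a larger randomized trial (1.1.2, 1.2), so a misleading FDG result could affect that choice.

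A separate, smaller point concerns RECIST: the preferred modality has no post-treatment diagnostic scan in the schedule.

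**Working it through.** **Is the pairing fixed by the protocol?** PERCIST class comes from FDG (5.5.2). TLG exists only for FDG (9.1), so the sentence in 9.3 cannot be read as covering the PD-L1 tracer alone. No section excludes FDG measures from the PERCIST comparison.

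**Size of the built-in association, direct calculation.** Assumptions not in the protocol: FDG % change is normal with mean 0, classes are cut at ±30%, and the SD is 20, 30 or 40 points. For a standard normal variable cut at ±c, with density φ(c) and upper-tail area T(c), the share of variance explained by the three classes is 2·T·(φ/T)² = 2φ²/T.

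| SD | c = 30/SD | φ(c) | T(c) | 2φ²/T | square root |
|---|---|---|---|---|---|
| 20 | 1.5 | 0.1295 | 0.0668 | 0.50 | 0.71 |
| 30 | 1.0 | 0.2420 | 0.1587 | 0.74 | 0.86 |
| 40 | 0.75 | 0.3011 | 0.2266 | 0.80 | 0.89 |

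Pathology does not enter this calculation.

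**Check at the planned sample size.** The protocol's own figure reproduces: 15 × 0.25 = 3.75, that is, 3 to 4 histopathological responders (1.1.2). In 2,000 simulated 15-patient studies per setting, FDG change was drawn independently of true response (4 responders, 11 non-responders). Classes were cut at an assumed ±15%, ±25% or ±30%, with an assumed SD of 30, 45 or 60 points. A second FDG measure equalled the same change plus 15-point noise, of the order of the roughly 15% test-retest variability in 9.2.1. This stands in for TLG or another SUV metric, which is not identical to the one classified.

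- Against PERCIST class: median Spearman correlation 0.74 to 0.90, with two-sided p < 0.05 in 93% to 100% of studies.
- Against pathological response (exact Mann-Whitney): p < 0.05 in 3.6% to 4.4% of studies.

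The protocol sets no alpha; 0.05 is used only as a yardstick.

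**Direction of the labels.** PERCIST limits are not printed. For an assumed mean rise m in responders, SD s of 20 or 30 points, and limit t of 15%, 25% or 30%, the share above the limit is 1 − Φ((t − m)/s) and the share in the response class is Φ((−t − m)/s).

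| Mean rise m | Progressive class | Response class |
|---|---|---|
| 20% | 31% to 60% | 1% to 12% |
| 40% | 63% to 89% | 0% to 3% |
| 60% | 84% to 99% | 0% to 1% |

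Example: m = 40, s = 30, t = 30 gives 1 − Φ(−0.33) = 0.63 progressive and Φ(−2.33) = 0.01 response. At m = 20 the remainder, labelled stable, runs from 1 − 0.57 − 0.12 = 0.31 to 1 − 0.31 − 0.01 = 0.68. Under these assumptions few true responders carry a response label, but whether they are called stable or progressive depends on the size of the rise and the limit.

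**Which comparisons in 9.3 are affected?**

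| Predictor | PERCIST | RECIST 1.1 | Mandard grade |
|---|---|---|---|
| % change in FDG SUV, TLG | circular | not circular | not circular |
| [18F]BMS-986192 SUV | not circular | not circular | not circular |

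**RECIST modality.** Diagnostic CT: baseline only (7.12, 7.19). Head-and-neck MRI: baseline and just before surgery (3.5, 7.12, 7.19). The only repeat CT is the low-dose attenuation scan with each PET (5.3). The paired anatomical scan is therefore MRI, while Appendix 1 names CT.

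**The case against.** The strongest reply is that the comparison that matters is already planned. Section 1.2.2 names histopathological response as what the FDG rise should predict, and 9.3 lists Mandard grade and RECIST beside PERCIST. The study is a 15-patient pilot, described in 4.3 as descriptive and hypothesis-generating, with no alpha or decision rule. No section ties surgery or adjuvant treatment to PERCIST class. Nor do the two problems add up to a false confirmation of 1.2.2: the circular comparison would link an FDG rise with progression, the opposite of what 1.2.2 predicts, and could support only the non-directional wording of hypothesis 5.

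Most of this stands, and it limits the point. A reader might infer more than the protocol supports:

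- *That the whole early-response analysis is circular.* Early response is also read on MRI, and only FDG change against PERCIST shares its data.
- *That responders will be classed as progressors.* The limits are not printed, only rises beyond them would be so labelled, and the expectation of a rise is itself hedged in 1.2.7.
- *That RECIST cannot be assessed.* CT is preferred in Appendix 1, not required, and paired MRI is scheduled.
- *That Mandard grade must be the sole reference.* That would discard the valid RECIST comparison.

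The reply does not rescue the FDG-change-by-PERCIST comparison. A descriptive correlation of a variable with its own categories still misleads, and the protocol itself, not an unseen analysis plan, fixes the pairing.

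**Conclusion.** The point holds for one comparison. Correlating % change in FDG SUV and TLG with PERCIST class is circular as written: about 50% to 80% of variance explained without any relation to tumor response, assuming limits of ±30% and an SD of 20 to 40 points. The simulation over other assumed limits and SDs agrees. The exact figure depends on those assumptions; the circularity does not.

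The conflict of labels is conditional. If FDG rises early in responders, PERCIST would call them progressive or stable according to the size of the rise, and the protocol does not say how to read this. The harm is to the interpretation of a secondary result, not to a formal error rate, so this is a should-fix. The CT/MRI mismatch is a minor inconsistency, independent of the circularity.

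**What to change.** - **9.3 and 6.2:** remove the correlation of FDG change measures with PERCIST class. Make Mandard grade the main reference for FDG change, as 1.2.2 already expects, and keep the planned RECIST comparison. Leave [18F]BMS-986192 uptake against PERCIST as it is.
- **9.3:** analyse FDG change as a continuous, two-sided predictor, with increase stated as the expected direction in responders.
- **PERCIST:** report it descriptively, cross-tabulated against Mandard grade, with a sentence on how an early FDG rise is to be interpreted.
- **Appendix 1:** reconcile the CT preference with 3.5, 7.12 and 7.19, where the paired pre- and post-nivolumab anatomical scan is head-and-neck MRI.

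Cost: wording only. All scans and pathology grades are already planned; no new data are needed.

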We hypothesize that neoadjuvant treatment with PD-1 inhibitor nivolumab will lead to antitumor immune activation and improved clinical outcome in advanced stage oral cancer patients scheduled for curative surgery. To prove these hypotheses a randomized controlled trial (RCT) should be designed, but the combination of neoadjuvant immunotherapy, extensive surgery and (when indicated) postoperative combination treatment with chemoradiation may lead to potentially unforeseen complications. Therefore, this study was designed to evaluate safety and tolerability of neoadjuvant nivolumab and investigate potential biomarkers for response that could be evaluated in a larger RCT. Based on the studies and efficacy of nivolumab in the recurrent/ metastatic setting, we anticipate in a study of 15 patients at least 3-4 patients (~25%) with a (histopathological) response in the resection material, likely coinciding with immune activation in the tumor.

Please see the nivolumab Investigator Brochure [32] for the full preclinical and clinical data.

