## Tumor imaging and assessment of disease

Besides the [^18^F]BMS-986192 and [^18^F]-FDG PET scans, a baseline MRI of head and neck will be made for baseline tumor measurements. Early response evaluation with MRI will be performed just before surgery (day 24 ±3, [Figure 1](#Figure1)). As included in standard of care, a diagnostic CT of neck, thorax and abdomen will be performed before treatment.

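### Section 9.3 relates PET uptake to anatomical imaging response only through RECIST classes, although paired MRI gives a continuous change in tumor size that 15 patients can ill afford to lose

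*Protocol*

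**What the plan says.** Section 9.3 sets out the analysis in one sentence: "The correlation between the continuous variable SUV, the % change in SUV and TLG and the categorical variables response on imaging". That sentence defines imaging response by class, "the categorical variables response on imaging (according to RECIST 1.1 CR, PR, SD, PD", together with the four PERCIST classes. The same sentence adds "pathological response (according to the Mandard Classification System, Table 3) will be assessed". No continuous response measure is listed and no test is named.

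The raw material for a continuous measure is planned. Section 7.12 says that "a baseline MRI of head and neck will be made for baseline tumor measurements", and schedules a second MRI just before surgery. Section 3.5 gives the purpose of the pair as evaluating response to nivolumab. The diagnostic CT is scheduled only before treatment, yet Appendix 1 names CT as the preferred technique for RECIST.

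On size and purpose, Section 4.3 states that "a sample size of 15 evaluable patients has been chosen", that "no formal statistical justification for the sample size is provided" and that "The objective of this study is descriptive and hypothesis generating". Section 1.1.2 anticipates "at least 3-4 patients (~25%) with a (histopathological) response in the resection material". No alpha, power or expected correlation is given.

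**The concern.** A RECIST class is a coarse cut of the change in tumor size. Relating a continuous PET measure to the class treats all patients within a class as identical. After one dose and about three weeks, most of 15 patients could share a class. The comparison would then rest on a handful of patients, or on none.

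Section 1.2.7 gives the aim of the PET work as identifying biomarkers for response, and Section 1.1.2 says promising ones could be evaluated in a larger randomized trial. At stake is how clearly these 15 patients can show whether PD-L1 or FDG uptake tracks tumor shrinkage. The patients and scans are the same on either scale; only the choice of variable differs.

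**Working it through.** **Inputs from the protocol.** n = 15 (4.3). Expected histopathological response about 25% (1.1.2). Response rate 13.3% in recurrent/metastatic disease (1.1.3). In small neoadjuvant studies, 25-40% response and tumor shrinkage in 40-50% (1.1.2).

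**Assumptions.** Two-sided alpha 0.05; true correlation rho between the PET measure and size change of 0.5, 0.6 or 0.7; bivariate normality; class shares as listed below. The protocol gives none of these. Applying the 25% to RECIST is also an assumption, because it is a histopathological rate.

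**1. The protocol's own figure.** 15 × 0.25 = 3.75, consistent with 3-4 responders. Binomial: P(at least 3) = 0.764; P(at most 1) = 0.080. The sample size itself cannot be reproduced, as no calculation is given.

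**2. How empty could a class be?** At 13.3%, P(0 of 15) = 0.867^15 = 0.118. P(at most 1) = 0.118 + 15 × 0.133 × 0.867^14 = 0.118 + 0.271 = 0.388 (unrounded sum). If 10% shrink, 80% are stable and 10% progress, about 3% of trials have all 15 patients in one class.

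**3. Power on each scale.** Size change y is standard normal, and the PET measure is x = rho·y + √(1 − rho²)·e, with e independent standard normal. y is kept continuous, or cut at the quantiles that give the assumed shares.

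Continuous size change at rho 0.5 / 0.6 / 0.7: Spearman 44 / 62 / 81%, Pearson 50 / 70 / 87%.

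| Assumed RECIST shares | Test | Power, % | Loss against Spearman, points |
|---|---|---|---|
| 13.3% responders, rest | t test | 20 / 27 / 37 | 24 / 35 / 43 |
| 25% responders, rest | t test | 27 / 39 / 53 | 17 / 24 / 28 |
| 40% responders, rest | t test | 32 / 46 / 63 | 12 / 16 / 18 |
| 50% responders, rest | t test | 33 / 47 / 64 | 11 / 15 / 17 |
| CR/PR/SD/PD 2/23/60/15 | ANOVA | 28 / 42 / 62 | 16 / 20 / 19 |
| CR/PR/SD/PD 2/23/60/15 | ordered (rank) | 37 / 52 / 71 | 7 / 10 / 10 |
| about 0/10/80/10 | ANOVA | 24 / 34 / 49 | 20 / 28 / 32 |
| about 0/10/80/10 | ordered (rank) | 25 / 36 / 50 | 19 / 26 / 31 |

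Losses come from unrounded values and carry about one point of simulation error. A Kruskal-Wallis test on the classes does worse still: 12 / 19 / 29% for 0/10/80/10. Part of that is its conservatism at this sample size (about 2% rejection under no association).

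**4. What the continuous analysis can and cannot do.** Using Fisher's z with SE = 1/√(15 − 3) = 0.289, an observed correlation of 0.5 has limits tanh(0.549 ± 1.96 × 0.289), or −0.02 to 0.81. Power of 80% needs a true correlation of tanh((1.96 + 0.84)/√12) = 0.67.

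**5. Mandard grade.** With assumed shares of 7/8/10/35/40% in TRG 1-5, power is 24 / 35 / 54% by ANOVA and 40 / 56 / 75% by rank correlation. With 10/15/20/30/25% it is 23 / 36 / 56% against 42 / 59 / 79%. Ignoring the order costs about 16 to 23 points. Keeping it leaves power within about 2 to 6 points of the continuous rank analysis.

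**The case against.** Five objections deserve weight.

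- **Power is not this protocol's standard.** It calls itself descriptive and gives no alpha or target. This stands. A reader might infer that the trial misses a design goal; it has none to miss. The loss matters only as information thrown away.
- **The size of the loss rests on assumptions.** This stands too. A reader might infer that the loss is large whatever happens. It is not: an ordered test on a reasonable spread of classes loses as little as 7 points, and a 40-50% split loses about 11 to 18. No row of the table shows zero loss, however.
- **Mandard grade matters more than RECIST, and nothing is wrong with it as written.** The response hypotheses do centre on pathology. A reader might infer from the word categorical, from the ANOVA in 9.4, or from the No regression label beside TRG 4 in Table 3 that the grades will be analysed as unordered or that TRG 4 and 5 will be pooled. The text does not say so. Section 9.3 names no test, the ANOVA in 9.4 is for PD-1 and PD-L1 staining, and Table 3 keeps the two grades on separate, separately defined rows. Only a clarification is warranted.
- **Continuous response information is not absent everywhere.** Correct: Section 6.2 correlates the continuous uptake of both tracers, and FDG change serves as an early readout. The point is confined to anatomical imaging response in 9.3.
- **The relation may not be linear.** Section 1.2.2 expects immune activation to raise FDG uptake in responders. A rank correlation removes the need for linearity but still assumes a monotone relation.

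**Conclusion.** The point holds for RECIST. Section 9.3 fixes anatomical imaging response as a class, although the scheduled MRI pair gives a continuous size change. For true correlations of 0.5 to 0.7 and the class shares tried, the t test, ANOVA and ordered tests in the table lose roughly 7 to 43 points of power against Spearman's correlation on the continuous change. The correlations and shares are assumptions, not protocol figures. In a descriptive study of 15 the consequence is a weaker and less precise biomarker signal. Even the better analysis will give wide intervals. The change is worth making because it costs almost nothing, not because the design fails without it.

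For Mandard grade there is no error, only an ambiguity worth closing.

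**What to change.** In Section 9.3:

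- Add the percentage change in the sum of tumor diameters on the paired MRI scans, baseline to pre-surgery, as the lead imaging-response correlate. Report Spearman's rho with a 95% confidence interval against baseline SUV, percentage change in SUV and percentage change in TLG.
- Keep the RECIST classes as descriptive tables.
- As a clarification, state that Mandard TRG 1-5 is analysed as an ordered score by rank correlation.

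In Appendix 1, reconcile the stated preference for CT with the MRI-based measure. Without this the new correlate conflicts with the appendix.

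The cost is wording in two places. No scan, patient or pathology reading is added, and assigning RECIST classes on the MRI pair would need the same diameters. The small downside is that RECIST class is no longer the lead correlate, although it is still reported.
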